### Participants and Data Collection

The subprojects will be informed by a systematic literature review performed before the project (manuscript forthcoming).

*Subproject 1:* KVB claims data will be used for the analysis. The KVB data includes all claims for ambulatory physicians in the State of Bavaria made by insured persons residing in Bavaria. The analysis is based on the *Bavarian COVID-19 Cohort* which was established from anonymized billing records of all patients with statutory health insurance in Bavaria. Both general practitioners and medical specialists submit details on patient encounters, including treatments, diagnoses, and billing information, to the KVB in each quarter. The dataset includes pseudonymized patient identifiers, demographic variables (age, sex, region), diagnoses (International Classification of Diseases, 10th Revision, ICD-10 codes with diagnostic certainty) and billed services (EBM codes, specialty, and practice identifiers). This structure allows longitudinal tracking of health care utilization, comorbidities, and treatment patterns across cohorts.

Out of 9,202,930 individuals with any respiratory infection, 4,247,455 had a confirmed COVID-19 diagnosis and the remained any other respiratory infection. For the analysis, three cohorts were randomly drawn:

COVID-19 (2020–2022): 196, 000 individuals with a confirmed diagnosis of COVID-19, ie, *ICD* codes U07.1 or U08.9 or U09.9 (secured and suspected diagnoses)Control (2020–2022): 140,000 individuals matched to the COVID-19 cohort by age and sex who received a confirmed ambulatory diagnosis of a respiratory infection (*ICD* J00*–J22*, J40*–J42*) in the same quarter.Historical control (2019): 140,000 individuals with a confirmed respiratory infection (*ICD* J00*–J22*, J40*–J42*) diagnosed in 2019, matched by age and sex to the COVID-19 cohort

*Subproject 2:* Patients with PCC will be asked to participate in individual interviews about their experiences with health care delivery. Inclusion criteria comprise adult patients from the Munich region and the wider Bavaria area who either have a confirmed diagnosis of PCC or self-report having experienced PCC in the past or currently. Participants must have received or be receiving ambulatory treatment. Recruitment will be conducted through PCC support groups in Munich. These groups bring together individuals affected by PCC who meet regularly to exchange experiences and provide mutual support. A semistructured interview guideline will be developed and tested, taking into account individual experiences and care processes. Findings from the systematic review will be incorporated into the development of the guidelines. The guideline will establish a thematic framing and consists of all relevant topics that need to be addressed in the interview. It ensures better comparability of the data and structures the entire communication process [29]. Potential interview partners for the qualitative part of the project will be recruited utilizing a snowball sampling approach wherever possible [30]. This process follows the principle of maximum variation, aiming to capture a diverse range of perspectives and experiences. The qualitative interviews and the focus group will be conducted in person or via video conference. During the interview, patient journey maps will be developed [31,32]. The number of interviews is determined according to the methodological criterion of theoretical saturation [33]. The sample is expected to consist of around 20 to 25 participants. Should saturation be achieved earlier, indicated by the emergence of no new themes, a reduced number of interviews will be conducted. Conversely, if saturation is not attained, the sample size will be stepwise increased until the required number is reached.

The study will include a focus group, comprising 5‐10 participants. The discussion will take place face-to-face in a university meeting room and will be facilitated by two researchers. If an in-person participation is not possible due to severeness of disease, an additional online-based option will be made available. Results of both the data analysis and the synthesis of the individual interviews will be presented. Discussions will follow a semistructured guide with open-ended questions and are planned to last between 60 and 90 minutes. Participants will be selected from the pool of individuals who previously took part in the individual interviews, applying the same inclusion criteria. Recruitment will occur through renewed email contact. Group composition will be arranged to allow discussion of both shared and divergent care experiences. Participation will be voluntary, with withdrawal possible at any time without consequences. Before the discussion begins, sociodemographic information will be collected and written informed consent for participation and audio recording will be obtained on site. The moderator will lead the discussion, while the co-moderator will oversee time management, observe group dynamics, and take field notes. Data will be collected through audio recordings supplemented by field notes. All data will be pseudonymized, and deleted after transcription is completed.

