## Introduction

According to the World Health Organization, more than 770 million people worldwide have been infected with Severe Acute Respiratory Syndrome Coronavirus 2 (SARS-CoV-2), with approximately 6.9 million deaths [1]. While symptoms often subside within 14 days, many patients continue to have symptoms after the acute illness [2,3]. The generally used term ‘long COVID,’ medically described as *post-COVID-19 condition* (PCC) is defined as the presence of symptoms that persist or newly develop three months after a SARS-CoV-2 infection and last for at least two months without an alternative explanation [4]. The symptoms experienced by patients with PCC are highly diverse and reflect the multifaceted nature of the condition. These symptoms can affect multiple systems of the body, further highlighting the complexity of the condition [3,5,6]. However, there are certain symptoms that occur more frequently. These include fatigue, myalgia, neurological symptoms such as cognitive impairment, loss of smell and taste, as well as headaches, mental health issues, including depression and anxiety, and cardiopulmonary symptoms like dyspnea, chest pain, and palpitations [5,7-11].

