### Study Design

The study follows a convergent mixed-methods design aiming to describe and analyze the trajectories of patients following an acute SARS-CoV-2 infection in the ambulatory setting (see Figure 1). Quantitative analyses of statutory health insurance claims data and qualitative interview analyses will be conducted in parallel and independently. Data and results from two subprojects will be used to facilitate the synthesis.

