### Data Analysis

#### Subproject 1

For the claims data, control groups will be matched by age, gender, and time of diagnosis (year/quarter). We will analyze the utilization patterns longitudinally for the cohorts and will focus specifically on the health care service billing group. We will estimate the incidence of PCC diagnoses (*ICD* codes: U09.9, U07.4), as well as newly occurring comorbidities, which may also be in the context of PCC. Expected outcomes are: (1) SARS-CoV-2 related symptoms, (2) newly developed diseases (cardiovascular diseases, autoimmune diseases, mental health diseases). Here, a special focus will be on diseases related to PCC, irrespective of a specific PCC diagnosis (eg, ICD-10 codes: R53, G93.3, F06.7, R43, M79.1, I26, R05, F48.0, F41) [4,34]. Health care utilization is analyzed using a *State Sequence Analysis* (SSA) [35]. Analyses are conducted for the cohort of SARS-CoV-2 infections and the control groups. In the analysis, the health care utilization for primary and specialist care as well as their respective diagnoses will be analyzed in the time before and after the SARS-CoV-2 infection. A specific focus will be on the appearance of a PCC diagnosis or diagnoses of PCC-related conditions. SSA identifies individual care trajectories represented as ordered sequences of quarterly states, where each state reflects contacts with general practitioners, COVID-19 specialists, or other specialists. Dissimilarities between trajectories are quantified using a theory-driven cost matrix, and clusters of patients with similar utilization patterns are derived through an unsupervised medoid-based clustering procedure. The optimal number of clusters is selected based on established quality indices (eg, average silhouette width). Factors associated with the resulting care pathway clusters are subsequently analyzed using multivariable regression models.

Additionally, the potential health care utilization depends on regional factors. Therefore, the place of residence of the cohort is recorded at the level of the districts and independent cities of Bavaria as well as the degree of urbanization of the municipality of residence. The regional distributions of the cohort and utilization patterns are visualized and analyzed using *geographical information systems* (GIS). Differences are analyzed using hierarchical regression models.

#### Subproject 2

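### U09.9 is both a sufficient entry code for the COVID-19 cohort and a counted PCC outcome, so patients first coded U09.9 are cases by construction and raise the estimated PCC incidence

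*Protocol article*

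**What the plan says.** Under Participants and Data Collection (Subproject 1), the Protocol article describes the COVID-19 cohort as "196, 000 individuals with a confirmed diagnosis of COVID-19", defined by "codes U07.1 or U08.9 or U09.9 (secured and suspected diagnoses". The codes are joined by "or", so any one of them is enough. The cohorts are described as already drawn.

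Under Data Analysis (Subproject 1), the article states: "We will estimate the incidence of PCC diagnoses", with "codes: U09.9, U07.4), as well as newly occurring comorbidities". The outcome list is therefore U09.9 and U07.4. On the sequence analysis it adds: "A specific focus will be on the appearance of a PCC diagnosis or diagnoses of PCC-related conditions".

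The intended time anchor is the acute infection. Study Design speaks of "trajectories of patients following an acute SARS-CoV-2 infection in the ambulatory setting", and Data Analysis says that utilization and diagnoses "will be analyzed in the time before and after the SARS-CoV-2 infection". The same section matches controls on age, gender and the year and quarter of diagnosis. The Introduction defines PCC as "symptoms that persist or newly develop three months after a SARS-CoV-2 infection and last for at least two months without an alternative explanation".

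The article states no requirement of an earlier U07.1, no separation of prevalent from incident PCC, and no rule for dating the infection when no acute code is on record. The limitations in the Discussion mention coding and date inaccuracy in general, but not this overlap.

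**The concern.** A code that admits a patient to the population at risk should not also be the event counted in that population. A patient who enters on U09.9 was never at risk of a first PCC diagnosis within the cohort; that patient already has one. Such patients add to numerator and denominator alike, and the proportion can only rise.

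There is also a timing problem. If the only COVID code on record is a post-COVID code, the quarter of diagnosis available for matching is likely to be later than the quarter of infection. Three things would follow for these patients:

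- their period before the index would contain the acute illness and perhaps early PCC care;
- their quarterly state sequences would start late relative to infection;
- they would be compared with controls who are at the diagnosis of a respiratory infection in that quarter.

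PCC is the declared focus of the study and the results are meant to inform care planning, so the PCC incidence and the infection-anchored pathways are central outputs.

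**Working it through.** The article gives no incidence or power figure on this point, so there is nothing to reproduce. The check has three steps.

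**1. Code lists side by side**

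| Code | Admits to COVID-19 cohort | Counted as PCC outcome |
|---|---|---|
| U07.1 | yes | no |
| U08.9 | yes | no |
| U09.9 | yes | yes |
| U07.4 | no | yes |

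The overlap is U09.9 alone. Listing it as an alternative entry code changes cohort membership only by adding patients with neither U07.1 nor U08.9. Either it adds nobody, or it adds patients who are cases on entry. Such patients are plausible: the data hold ambulatory physician claims only, so an infection diagnosed elsewhere leaves no U07.1.

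**2. Direction and illustrative size of the incidence bias**

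Let *e* be the share of the cohort whose first COVID code is U09.9, and *i* the proportion with a PCC code among everyone else. Then

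crude = e × 1 + (1 − e) × i, and relative overstatement = (crude − i) / i = e(1 − i) / i.

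This is positive for every e > 0. Neither *e* nor *i* is in the article; the values below are assumptions. The first column also shows e × 196,000.

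| e (patients) | i = 2% | i = 5% | i = 10% |
|---|---|---|---|
| 0.1% (196) | 2.10% (+4.9%) | 5.10% (+1.9%) | 10.09% (+0.9%) |
| 1% (1,960) | 2.98% (+49%) | 5.95% (+19%) | 10.9% (+9%) |
| 3% (5,880) | 4.94% (+147%) | 7.85% (+57%) | 12.7% (+27%) |
| 5% (9,800) | 6.90% (+245%) | 9.75% (+95%) | 14.5% (+45%) |

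Worked example: e = 3%, i = 5% gives 0.03 + 0.97 × 0.05 = 0.0785, and 0.0785 / 0.05 = 1.57.

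The sign is settled by the algebra. The size is not: the table runs from negligible to more than a tripling.

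**3. Timing**

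Take the Introduction's definition as a guide to when U09.9 is coded, and assume that infections are spread evenly over a quarter. A code given exactly 3 months after infection falls one calendar quarter later for every infection date. A code given at 3 + 2 = 5 months falls one quarter later for infections in the first third of the quarter and two quarters later for the other two thirds. On quarterly states, that is a shift of one or two positions. This is indicative only, because the definition is clinical and is not a coding rule.

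**The case against.** The strongest reply is that this is a condensed article. Incidence ordinarily means new cases, and an unseen full protocol or analysis plan may exclude prevalent cases or re-date them. No index rule is stated, and the article names the infection as its anchor. Admitting PCC patients without a coded acute infection may also be deliberate in a study of PCC care. Finally, the size of the bias rests wholly on assumed inputs.

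Much of this stands. It limits the point in four ways.

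- A reader might infer that U08.9 is also both entry code and outcome. It is not: the outcome codes are U09.9 and U07.4.
- A reader might infer that the article fixes a wrong index quarter. It fixes none. The misalignment is inferred from matching on the quarter of diagnosis where no acute code exists, and so is probable rather than shown. The Introduction's three-month interval does not establish a fixed lag for every U09.9 claim, since the Discussion itself warns of inaccurate codes and dates.
- A reader might take the whole cohort to be affected. Patients with an earlier U07.1 are not, provided they are indexed on it.
- A reader might take one of the percentages above as an estimate. None is, and a very small bias is not excluded.

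What the reply does not remove is the overlap itself. The entry rule and the outcome codes are both stated, and the cohorts were drawn under that rule. This is a stated definition that misleads if applied as written, not a detail left out for brevity. A wish to keep PCC patients for describing care pathways is reasonable, but it is no reason to keep them in an incidence denominator.

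**Conclusion.** The point holds for the PCC incidence. As the Protocol article is written, patients whose first COVID code is U09.9 are PCC cases by construction, and the estimate is too high whenever there are any. U08.9 contributes to entry, and hence to timing, but not to the numerator.

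For patients first coded U09.9 or U08.9, the before/after comparison and the infection-aligned sequences are likely misaligned. This rests on two assumptions: that the quarter of diagnosis serves as their index, and that these codes are usually given after the quarter of infection.

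The magnitude cannot be obtained from the article. It depends on the share of such patients, which the study team can count in the data already delivered.

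**What to change.** For the incidence, before/after and infection-aligned sequence analyses:

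1. Set cohort entry and the index quarter by the first U07.1, and count U09.9 and U07.4 only after that quarter.
2. Take patients whose first COVID code is U09.9 or U08.9 out of these main analyses. Report their number and describe their care as a separate group with unknown infection date, since PCC care is the study's focus.
3. Add a sensitivity analysis that includes them.
4. Recheck the balance of the controls on age, sex and quarter against the restricted cohort, and redo the matching if needed. Simply deleting these patients' matched controls is not an available step on what is stated: with 196,000 cases against 140,000 in each control cohort, no ratio or pair link is established.

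The cost is a filter on codes that the dataset already holds, a sentence in the protocol or analysis plan, and possibly a new match. The main analysis cohort falls somewhat below 196,000, and PCC patients without a coded acute infection leave the main estimates. Further analyses are scheduled until April 2027, so the change is still feasible; it is best made before any PCC incidence is reported.

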**Figure 1. F1:**
[figure not shown]
Mixed-methods study approach.

First, in a retrospective cohort study with claims data (Subproject 1) objective care pathways will be reconstructed based on routine data from the KVB. To do so, three cohorts will be defined, a cohort of patients with SARS-CoV-2 infection and a cohort of patients with other respiratory tract infection during the pandemic phase 2020 till 2022. To measure the impact that the pandemic had on the overall health care utilization, we will also form a historic control group with respiratory tract infections in the year 2019.

Second, a qualitative study (Subproject 2) will be conducted, including semistructured interviews with people affected by PCC concerning their individual subjective experiences and personal motivations for (non-) utilization of care.

The integration of the results will take place at the interpretation stage through systematic triangulation. Quantitatively identified care pathways will be compared with themes derived from patient interviews to identify areas of convergence, complementarity, and divergence. Joint displays will be developed that compare quantitative care trajectories with qualitative interview data, enabling structured comparisons across data sources. This will be achieved by using the software MAXQDA (version 24.9.1), as referenced by Kuckartz [27,28].

All results will be synthesized in a focus group in order to record and understand the care processes holistically and to classify them in the light of the existing evidence. The focus group will serve to validate and refine the results of the individual interviews, to contrast individual experiences within a group setting, and to enable in-depth exploration of shared experiences and interpretive patterns. Moreover, it supports the development of evidence-informed recommendations for care improvement. The synthesis will be published in scientific journals and made accessible to affected individuals and care providers to ensure broad dissemination and practical impact.

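### The COVID-19 cohort is called confirmed but defined to include suspected diagnoses, while both control cohorts are described as confirmed only

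*Protocol article*

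**What the plan says.** The cohort definitions are in the protocol article under Participants and Data Collection, Subproject 1.

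- **COVID-19 cohort, 2020–2022:** "196, 000 individuals with a confirmed diagnosis of COVID-19". An i.e. then introduces the codes U07.1, U08.9 and U09.9, and the list closes "U08.9 or U09.9 (secured and suspected diagnoses".
- **Concurrent control, 2020–2022:** 140,000 matched people "who received a confirmed ambulatory diagnosis of a respiratory infection" in the same quarter.
- **Historical control, 2019:** "140,000 individuals with a confirmed respiratory infection", matched by age and sex.
- **Source population:** of 9,202,930 people with any respiratory infection, "4,247,455 had a confirmed COVID-19 diagnosis".
- **Available data:** the dataset holds "ICD-10 codes with diagnostic certainty".

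The Study Design section, below Figure 1, names the exposed group as "a cohort of patients with SARS-CoV-2 infection". Data Analysis, Subproject 1, uses U09.9 again, together with U07.4, as a code for diagnosed post-COVID condition (PCC), and gives no certainty level there. The limitations in the Discussion concede general inaccuracy of ICD coding in billing data. They do not mention a certainty rule that differs between cohorts.

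**The concern.** The i.e. makes the code list the definition of the confirmed diagnosis, and that definition takes in suspected diagnoses. A reader cannot tell which rule drew the cohort. On the plain wording, the exposed cohort also has a lower certainty threshold than either comparator.

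A suspected COVID-19 code may belong to a patient whose infection was later excluded. If that patient had another respiratory infection, someone with the comparator condition is counted as exposed. Such a patient has no SARS-CoV-2 infection around which to arrange utilization before and after, and does not belong in the denominator for PCC incidence. The Discussion rests its conclusions on comparison with the control cohorts, so the entry rule bears on the main contrasts.

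**Working it through.** The article states no sample size, power or effect calculation, so there is no figure of its own to reproduce. The check is a comparison of the definitions, followed by a conditional illustration.

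**1. Definitions side by side**

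| Cohort | Label | Certainty stated |
|---|---|---|
| COVID-19, 2020–2022 (196,000) | confirmed | secured and suspected |
| Control, 2020–2022 (140,000) | confirmed | nothing beyond confirmed |
| Control, 2019 (140,000) | confirmed | nothing beyond confirmed |

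Grammatically, the parenthesis may govern all three codes or only U09.9. On either reading, suspected diagnoses enter under a confirmed label.

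**2. Concurrent contrast**

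Let s be the share of the COVID-19 cohort entering only by a suspected code, and p the proportion of those truly infected. Assume every secured case is truly infected. The uninfected share is then f = s(1−p).

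Let Δ be the true difference between infected people and concurrent controls, and δ the difference between uninfected suspected patients and those controls. Then:

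observed difference = (1−f)Δ + fδ

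If δ = 0, the relative loss is f = s(1−p). Neither s nor p is in the article, so the values below are assumptions.

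| s | p = 10% | p = 30% | p = 50% |
|---|---|---|---|
| 5% | 4.5% | 3.5% | 2.5% |
| 10% | 9% | 7% | 5% |
| 20% | 18% | 14% | 10% |
| 40% | 36% | 28% | 20% |

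In people, f × 196,000 gives 0.025 × 196,000 = 4,900 at the low end, 0.14 × 196,000 = 27,440 at s = 20% and p = 30%, and 0.36 × 196,000 = 70,560 at the high end. If uninfected suspected patients use more care than controls (δ > 0), for example through extra work-up, the loss is partly or wholly offset.

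**3. Contrast with 2019**

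The historical group is there to show the pandemic's effect on overall utilization; call that effect π. With δ = 0, the true contrast is Δ + π and the observed contrast is (1−f)Δ + π. The shift is −fΔ, but its relative size depends on π. With Δ positive, if π is negative and larger in magnitude than Δ, the contrast moves away from zero. So s(1−p) does not describe this contrast.

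**4. PCC incidence**

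Let I be the incidence among infected members and q the proportion of uninfected members counted as having PCC.

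observed incidence = (1−f)I + fq

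This is below I if q < I and above it if q > I. U09.9 is both an entry code and an outcome code. If a suspected U09.9 also counts as an outcome, people admitted by it join numerator and denominator together, and incidence could rise.

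**5. Sequence clusters**

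Clustering of trajectories is not a difference in means. Neither formula predicts how misclassified members would change the clusters.

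**The case against.** The strongest reply is that the asymmetry is inferred. The authors' own i.e. equates confirmed with secured and suspected. If they use the word loosely there, they may use it loosely for the controls too, and the rule could be the same in all three cohorts. If they use it strictly, the parenthesis may be the slip. This stands: the text does not show which rule was run. It does not remove the contradiction, because each of these explanations needs a correction to the text.

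Second, the parenthesis may attach to U09.9 alone. A suspected U09.9 may express doubt about PCC rather than about the earlier infection. This also stands: p could then be high, and the route through an excluded acute infection largely falls away. The mismatch with the confirmed label remains.

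Third, a reader might infer that uninfected people do dilute the exposed cohort and that every COVID-19 contrast is pulled toward zero. The article does not support that. It gives no share of suspected-only entrants, attenuation is expected only for the concurrent contrast and only if δ is near zero, and the direction elsewhere is open. A drift over calendar time would need certainty coding to have changed between 2020 and 2022, which the article does not report.

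Fourth, a sensitivity analysis by certainty is often left to a fuller plan that is not shown here. That is fair as to the sensitivity analysis. The point, however, concerns an entry rule that the article states in two incompatible ways. The general caveat on ICD coding does not cover a threshold that differs by cohort.

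**Conclusion.** The point holds as a contradiction in a stated entry rule, with a conditional consequence. It is certain that the COVID-19 cohort is labelled confirmed and defined to include suspected diagnoses, and that the controls are worded as confirmed only. If the rule was applied as written, some people without SARS-CoV-2 infection may be in the exposed cohort.

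The expected effect is attenuation of the concurrent contrast by s(1−p). That rests on uninfected suspected patients using care like controls and on secured cases being truly infected. The 2.5% to 36% range only shows what the assumed inputs imply and is not an estimate for this study. The sponsor can count s from the certainty variable; p will remain an assumption. For the 2019 contrast, the clusters and PCC incidence, neither size nor direction can be derived.

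**What to change.** First, state which rule was used. If the reference to suspected diagnoses is a slip, one corrected line settles the matter. If it is the real rule:

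- Apply the same certainty rule to all three cohorts, and say whether it covers every code or only U09.9.
- In the primary analysis, use secured codes only, both for entry and for U09.9 as an outcome.
- Keep suspected-only patients for one labelled sensitivity analysis, and report their number by quarter.
- State whether the source count of 4,247,455 was made under the mixed rule.

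The certainty variable is already in the data, and the Results section schedules further analyses until April 2027, so no new data are needed. The cost is more than a filter. The COVID-19 cohort becomes smaller, and some true infections coded as suspected are lost. Because the controls were matched to the COVID-19 cohort, balance on age, sex and quarter must be rechecked, with re-weighting if it has shifted.
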